### Secondary outcomes measures

2.11

Secondary measures will be assessed prior to the intervention (baseline), and at mid-treatment, 5-week follow-up (i.e., within 1-week of treatment completion and 5-weeks after commencement), and 2-month follow-up (i.e., 2-months after commencement) (see Table 1).

***Pain intensity and pain spread:*** Pain intensity will be assessed using a series of 0–10 NRS, where 0 = no pain, and 10 = worst imaginable pain. Average and worst pain over the past week and current pain will be assessed. A digital tablet (iPad; Apple, Cupertino, CA, USA), a digital stylus (Apple Pencil; Apple, Cupertino, CA, USA) and custom software will be used to obtain the pain drawings and assess pain extent as previously described [38]. The sketching software will display the frontal and dorsal views of the superior half of a body chart and participants will be asked to draw where they feel pain as precisely as possible. The pain extent (% of total body area) is determined by dividing the number of pixels shaded, by total pixels in the body chart areas. Only shaded pixels within the body perimeter are considered. Heat maps will be created to illustrate where pain was most frequently perceived at the four time-points. Heat maps are obtained by overlapping pain drawings from participants in each group, at each time point, and for back and front views.

***iTAD overall tactile acuity score:*** In addition to training tactile acuity, the iTAD also has two tactile acuity tests, measuring localisation and orientation accuracy that can be averaged in to an overall score^17 22^. The tests and procedures have been described previously ^17 22^. Latest data indicates that the overall score has good (ICC_2.1_ = 0.75) inter-rater reliability, with markedly less measurement error than TPDT (coefficient of variation at least 50% smaller) making it more sensitive to change [22].

### Exploratory outcomes and predictor variables

2.12

Exploratory outcomes are included primarily to inform a future trial and to better understand the iTAD device as a test of tactile acuity. Global perceived effect will be used to explore participant perceived effectiveness of the interventions at each outcome assessment timepoint. Participant will report overall improvement on an 11-point Global Perceived Effect (GPE) scale. The scale spans from −5 (‘much worse’) to 0 (‘no change’) to +5 (‘much better’). Participants who reported a change ≥ +3 at the final outcome assessment will be classified as ‘improved’ [39]. GPE scales are recommended for clinical research [40] and show excellent reliability [41]. The iTAD localisation and orientation sub-scores assessed at each timepoint will provide additional measures of tactile acuity. The Neck Disability Index will be used to explore changes in function [42].

Since the training effect may be affected by factors such as sleep, and psychological status, tactile acuity impairment, and hours training these variables will also be assessed and used as predictors in regression analyses. The Insomnia Severity Scale, Depression, Anxiety and Stress Scale, baseline tactile acuity scores, and training log data will be used to predict change in tactile acuity (for assessment timepoints see Table 1).

### Data analysis

2.13

The effect of training on tactile acuity will be assessed using a mixed-design two-way analysis of variance (ANOVA) with one between group factor with two levels (Group: iTAD and iTENS) and one repeated factor with four levels (Time: baseline, mid-treatment, 5-week and 2-month outcome assessment). While pain intensity and spread, disability and iTAD scores will be analysed with the same mixed-design AVOVA, the focus of interpretation will be to inform future sample size calculations, and selection of primary outcomes for future trials. For GPE scores, the percentage of people reaching our criterion for improvement (≥+3) will be calculated for each group for descriptive analysis. A multiple linear regression approach will be used to observe whether change in tactile acuity in the iTAD group is predicted by time spent training, baseline tactile acuity scores, baseline sleep (Insomnia Severity Index) and psychological status (Depression Anxiety Stress Scale). Where appropriate, results will be expressed in terms of statistical significance, effect size, descriptive statistics, and plots. Should the final data set contain >5% missing data for the primary outcome, a multiple imputation method will be used to replace missing values [43]. Rates of usual care modalities will be compared between groups in order to identify and discuss their possible influence.

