**Methods:**

and analysis: In this two-arm randomised clinical proof-of-concept trial we will recruit participants with neck pain receiving usual care physiotherapy in a secondary outpatient healthcare setting. Thirty-six participants will be randomised 2:1 to receive four weeks of either tactile acuity training using the Imprint Tactile Acuity Device (iTAD) or a placebo intervention, in addition to usual care. The placebo intervention will consist of a de-activated TENS machine (iTENS) said to deliver a sub-threshold inhibitory therapy. Outcomes will be assessed at baseline, mid-treatment, and at 5-weeks and 2-months follow-up. The primary outcome tactile acuity will be evaluated using the two-point discrimination test and locognosia tests. Feasibility will be informed by recruitment and attrition rates, adherence, credibility of the interventions, treatment satisfaction and blinding. Pain intensity and anatomical spread will be analysed as secondary outcomes. The effect of iTAD training on tactile acuity will be assessed using a 2 (Group: iTAD vs. iTENS) x 4 (Time: baseline, mid-treatment, 5-week and 2-month outcome assessment) mixed ANOVA. Secondary outcomes including pain and pain spread, will be analysed with a focus on informing sample size calculations in future trials.

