### Randomisation and concealment

2.3

A concealed stratified permuted block-randomized allocation approach will be employed [25], where participants are randomly allocated to the experimental or control group with a 2:1 ratio. The randomised allocation sequence will be generated using Microsoft excel by an experimenter not involved in data collection. To achieve low allocation predictability, while maintaining the allocation ratio, randomisation to group will occur in blocks of three (2:1) or six (4:2) allocations. The order of the blocks will also be randomised. Further, allocation sequences will be stratified by sex, to ensure equal proportions of males and females in each group. The allocation will be recorded on dark, non-transparent cards, and inserted into opaque envelopes that will be numbered consecutively. Envelopes will be inserted in separate boxes for each sex. After baseline testing, the experimenter will open a sealed envelope, pre-prepared by a third party, containing the participant's allocation.

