### Sample size

2.5

Previous single-armed trials investigating (manual) tactile training for patients with chronic pain found moderate to large effect sizes for within group change in tactile acuity (26% improvement, mean change: TPDT 17.1 mm, p < 0.01, Cohen's d = 1.06) [28] and pain intensity (22% improvement, mean change: VAS 1.0 cm, p = 0.02, Cohen's d = 0.55) [16]. We therefore expect that we need to reach at least medium-large effects in tactile acuity in order to mediate clinically meaningful changes in pain. However, these effect sizes are based on within-group change since a control group was not present. Nevertheless, similar size differences in change of pain intensity have been reported when comparing tactile acuity training to a control condition for: neck pain [29] (24% difference, Δ NRS 1.6 points, p = 0.02, Cohen's d = 0.44); back pain [29] (41% difference, mean change: NRS 2.3 points, p < 0.01, Cohen's d = 1.07); and phantom limb pain [30] (45% improvement, mean change: Multidimensional Pain Inventory 1.5 points, p = 0.02, Cohen's d = 1.16). However, since these studies did not include tactile acuity as an outcome measure, they are not directly informative for our primary research question. As such, a sample size calculation was performed to account for a >90% chance of finding a statistically significant (p < 0.05), medium-large ($\eta_{p}^{2}$ = 0.1) between-group difference in tactile acuity, using a within-between repeated-measures ANOVA with four time-points. The calculation estimated that 18 participants would be required. Accounting for a dropout rate which can be up to 20% for treatments involving active participation in people with health conditions [31,32] a pool of 24 participants (12 in each arm) were estimated to be necessary. To improve power to explore secondary outcomes, particularly within the tactile training group, the target sample size for the intervention arm was doubled (n = 24 intervention group; n = 12 control group).

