## Conclusion

4

If the current study shows improvement in tactile acuity relative to control, and if secondary data support the possibility of pain reduction, then there are significant potential benefits of continuing iTAD development and research. These include the prospect of a practical method of training tactile acuity and progress towards effective treatments for persistent pain. The trial results will be disseminated via publication in academic journals and presentation at academic conferences.

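### The primary 2 x 4 mixed ANOVA counts pre-randomisation baseline as an outcome level and gives no single baseline-adjusted difference between iTAD and iTENS

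*Protocol article*

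**What the plan says.** The abstract and section 2.13 (Data analysis) give the same model for the primary outcome. The abstract calls it a "2 (Group: iTAD vs. iTENS) x 4 (Time: baseline, mid-treatment, 5-week and 2-month outcome assessment) mixed ANOVA". Section 2.13 repeats this in words: the two arms form the between-group factor, crossed with "one repeated factor with four levels (Time: baseline, mid-treatment, 5-week and 2-month outcome assessment"). No baseline covariate, sex term, primary visit or directional contrast is named. Baseline acuity appears as a predictor only in the regression within the iTAD arm.

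Section 2.5 (Sample size) sizes the trial for a ">90% chance of finding a statistically significant (p < 0.05), medium-large" effect (partial eta squared 0.1), "using a within-between repeated-measures ANOVA with four time-points". It arrives at 18 participants, 24 after dropout, and finally 24 iTAD and 12 iTENS.

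Section 2.3 (Randomisation and concealment) states that "allocation sequences will be stratified by sex, to ensure equal proportions of males and females in each group", and that the envelope is opened after baseline testing. Section 4 (Conclusion) begins its case for further development with "If the current study shows improvement in tactile acuity relative to control".

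**The concern.** Treatment cannot affect a value measured before allocation, so baseline carries information about the participant and none about the effect of training. Treating it as an outcome level has two consequences.

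First, the Group x Time interaction is a joint test of three contrasts. It is significant for any difference in profile between arms: iTENS doing better, a difference at mid-treatment only, or iTAD improving. The decision in section 4 needs a direction, a size and a precision, and a later trial needs the same quantities for its planning. An omnibus F test supplies none of them.

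Second, change from an unadjusted baseline depends on whatever imbalance chance produces, and chance imbalance is not small with 24 and 12 participants. Adjusting for baseline removes that dependence and, when visits are only moderately correlated, gains power as well.

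**Working it through.** **1. The plan's own figure.** Inputs from section 2.5: partial eta squared 0.1, alpha 0.05, two groups, m = 4 visits. The correlation is not given, so rho = 0.5 is an assumption.

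- f² = 0.1/0.9 = 0.111, so f = 0.333.
- Group x Time interaction: lambda = f² N m/(1 − rho), with 3 and 3(N − 2) df.
- N = 18: lambda = 0.111 × 18 × 4/0.5 = 16.0 on 3 and 48 df, power 0.912. N = 16 gives 0.869, so 18 is the smallest even total.
- Dropout: 18/0.8 = 22.5, rounded up to 23 and made even for two arms = 24, as stated.
- Group main effect, lambda = f² N m/(1 + 3 rho): needs N = 62 at rho = 0.5.

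The stated 18 is therefore the interaction at rho = 0.5. With rho = 0.3 or 0.7 the interaction would need 24 or 12. That the interaction is the intended test is inferred from this match.

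**2. Chance baseline imbalance.** In SD units, the standard error of the baseline difference at 24:12 is √(1/24 + 1/12) = 0.354. With no treatment effect and a baseline difference b, the expected difference in change is −(1 − rho)b. For b = one standard error:

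- rho = 0.5: −0.5 × 0.354 = −0.18 SD
- rho = 0.7: −0.3 × 0.354 = −0.11 SD

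After baseline adjustment the expected value is zero. In simulated 24:12 trials without a treatment effect, the interaction test rejects in about 5% overall. Given a baseline difference of 0.7 SD (two standard errors), it rejects in 0.11 at rho = 0.5 and 0.09 at rho = 0.7.

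**3. Power of the planned test and of an adjusted 5-week difference.** Assumptions: compound symmetry, two-sided 0.05, and 19:10 analysed (24 × 0.8 = 19.2; 12 × 0.8 = 9.6). The effect is 0.8 SD at 5 weeks and 2 months and 0.4 SD at mid-treatment. The article states neither this effect nor this pattern.

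- n_h = 19 × 10/29 = 6.552.
- Interaction: lambda = n_h Σ(d_t − d̄)²/(1 − rho). With d = (0, 0.4, 0.8, 0.8), d̄ = 0.5 and the sum is 0.25 + 0.01 + 0.09 + 0.09 = 0.44. At rho = 0.5, lambda = 6.552 × 0.44/0.5 = 5.77 on 3 and 81 df.
- Adjusted 5-week difference: lambda = n_h d²/(1 − rho²). At rho = 0.5, lambda = 6.552 × 0.64/0.75 = 5.59 on 1 df.

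| rho | Interaction, 3 df | Adjusted 5-week, 1 df |
|---|---|---|
| 0.3 | 0.35 | 0.54 |
| 0.5 | 0.48 | 0.62 |
| 0.7 | 0.72 | 0.79 |
| 0.8 | 0.89 | 0.91 |
| 0.85 | 0.96 | 0.96 |

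Allowing also for the estimation of the baseline slope lowers the right-hand column by up to 0.02.

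With 0.8 SD sustained at all three post-baseline visits, the sum is 0.36 + 3 × 0.04 = 0.48. Power is then 0.52 versus 0.62 at rho = 0.5, and 0.92 versus 0.91 at rho = 0.8.

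**4. Sex.** In 4,000 simulated 24:12 trials with a sex effect of 0, 0.5 or 1.5 SD, constant over time, the interaction test had the same type I error (0.047) and the same power (0.63) each time. A constant sex effect cancels within person.

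**The case against.** The plan is consistent with itself. The trial is sized on the test that will be used, and at its own inputs (f = 0.333, rho = 0.5) that test has power 0.996 at 24:12 and 0.986 at 19:10. The interaction is a legitimate test of whether change differs by arm. Section 2.13 also promises effect sizes, descriptive statistics and plots, which would show direction. Follow-up contrasts and confidence intervals are often left to a statistical analysis plan, which is not shown. All of this stands, with two limits. The power just quoted corresponds to a sustained difference of about 1.54 SD and says little about smaller effects. And the model itself, with baseline as an outcome level, is stated rather than left open.

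A reader might infer more than the article supports:

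- **That the sample size is wrong.** It reproduces.
- **That false positives are inflated.** Overall type I error stays near 5%; the problem is conditional on the imbalance seen.
- **That leaving out sex wastes power.** It does not for the interaction, unless sex alters the time course.
- **That power is always lost.** The gain disappears at high correlation. Section 2.10 gives reliabilities of 0.85 for two-point discrimination and 0.86 to 0.92 for a similar locognosia test. These are at best upper guides to the correlation over two months, but they mean that the region of no gain cannot be excluded.
- **That averaging visits would be a safe way to gain more.** For a 0.8 SD effect seen only at 5 weeks, at 24:12 and rho = 0.5, an adjusted mean of the three post-baseline visits has power 0.20, against 0.62 for the interaction.

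**Conclusion.** The point holds as one of efficiency and targeting; no figure in the article is wrong. The stated primary analysis counts a pre-treatment value as an outcome, appears to rest on an undirected 3-df test, and gives no single estimate of the quantity on which continuation depends. Its result also varies with chance baseline imbalance, by about 0.18 SD in the change difference for a one-standard-error imbalance at rho = 0.5.

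For the ramped 0.8 SD effect at 19:10, the power advantage of the adjusted 5-week difference is 0.19 at correlation 0.3, 0.14 at 0.5, 0.07 at 0.7 and nil at 0.85; under a sustained effect it is marginally negative from 0.8 upwards. These figures assume compound symmetry and an effect size and pattern that the article does not give. The case for an adjusted, directed estimate with a confidence interval does not depend on them. The plan should be changed, but the trial is not invalid without the change.

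**What to change.** In section 2.13, for each tactile-acuity outcome (two-point discrimination and locognosia), analyse the post-baseline values in a linear mixed model with group, time, group x time, the baseline value of that outcome and sex; an ANCOVA of the 5-week value is the simpler alternative. Name the adjusted iTAD minus iTENS difference at 5 weeks, with its 95% CI, as the primary estimate, and state which sign means improvement, since a lower threshold and a higher percentage correct are the favourable directions. Keep the 2 x 4 ANOVA and the other visits as supportive. Sex belongs in the model because allocation is stratified by it.

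Table 1 already schedules the assessments, so only wording changes. The cost is two model degrees of freedom and commitment to one visit: an effect that shows mainly at another visit would appear only in the supportive results.

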### Treatment fidelity and progression

2.9

In order to aid adherence and ensure fidelity to protocol, participants will be contacted by the study clinician on a weekly basis during the 4-week intervention and participants will attend a mid-treatment outcome assessment in person. In the experimental group treatment is progressed automatically by increasing the difficulty of the tactile acuity games, the mid-treatment review will be used to implement a false progression of the placebo iTENS machine. Participants will also maintain a treatment log to record frequency and duration of treatment sessions. In the intervention group this will be cross-referenced to the iTAD software usage data for verification.

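### The iTAD-only regression of acuity change on baseline acuity is biased towards 'worse baseline improves more' and cannot tell this artefact from a training effect

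*Protocol article*

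**What the plan says.** Section 2.13 (Data analysis) of the protocol article plans a multiple linear regression to see whether "change in tactile acuity in the iTAD group is predicted by time spent training, baseline tactile acuity scores", together with the Insomnia Severity Index and the Depression Anxiety Stress Scale. Only the iTAD arm enters.

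Section 2.12 gives the reason: "Since the training effect may be affected by factors such as sleep, and psychological status, tactile acuity impairment, and hours training", these variables are measured and used as predictors. Table 1 lists them as exploratory predictors. Section 2.13 adds that, where appropriate, "results will be expressed in terms of statistical significance, effect size, descriptive statistics, and plots".

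The planned arms are "n = 24 intervention group; n = 12 control group" (section 2.5). Section 2.10 and Table 1 have two-point discrimination (TPDT) and locognosia measured at the same four times in every participant. Reliabilities are stated as ICC 0.85 (SEM 3.7 mm) for TPDT, 0.86 to 0.92 for a test similar to the locognosia task (both section 2.10), and 0.75 for the overall iTAD score (section 2.11).

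Neither section mentions a control-arm comparison, an interaction term or an allowance for regression to the mean in this regression.

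**The concern.** The question in section 2.12 concerns effect modification: does the benefit of training depend on how impaired a person is at the start? A benefit is a difference from what would have happened without training, so the question needs both arms. The model in section 2.13 has one.

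The outcome also contains the predictor. Baseline enters change with a minus sign, so a participant whose baseline reading was by chance too poor will tend to look improved, and one whose reading was too good will tend to look worse. The baseline slope is therefore negative in expectation without any training effect. The control participants would show the same slope, but they are excluded.

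At stake is the reading of one coefficient. Section 2.12 says that the exploratory outcomes serve mainly to inform a future trial. A finding that more impaired people respond better is the kind of result that such a trial might take up.

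**Working it through.** **The plan's own figure.** The article gives no figure for this regression. Its one sample size calculation, 18 participants for "a >90% chance of finding a statistically significant (p < 0.05), medium-large" effect in the mixed ANOVA, is reproduced as a group by time interaction: f² = 0.1/0.9 = 0.111, four times, an assumed correlation among repeats of 0.5, and noncentrality 0.111 × 18 × 4 / (1 − 0.5) = 16. Power is 0.912. That calculation says nothing about the regression.

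**Expected slope with no training effect.** Let B and F be baseline and follow-up on the same measure, with equal variance σ² and correlation r, and let C = F − B.

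- Cov(C, B) = rσ² − σ² = −(1 − r)σ², so the slope of C on B is −(1 − r).
- Var(C) = 2(1 − r)σ², so corr(C, B) = −√((1 − r)/2).

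For TPDT (r = 0.85) the slope is −0.15 and the correlation −√0.075 = −0.27. The SEM implies an SD of 3.7/√(1 − 0.85) = 9.55 mm. A participant one SD worse than the arm mean at baseline is then expected to gain 0.15 × 9.55 = 1.4 mm more than an average participant, with no training effect.

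**How often it looks significant.** The null model was simulated with four predictors (training time, baseline, sleep, one psychological score), the other three taken as independent of acuity. Completers number 24, or 19 if dropout reaches the figure in section 2.5 ("a dropout rate which can be up to 20" per cent; 24 × 0.8 = 19.2). There were at least 20,000 trials per setting.

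| r used | Source | Slope | p < 0.05, n = 24 | p < 0.05, n = 19 |
|---|---|---|---|---|
| 0.92 | locognosia, upper | −0.08 | 14% | 11 to 12% |
| 0.86 | locognosia, lower | −0.14 | 21 to 22% | 17% |
| 0.85 | TPDT | −0.15 | 22 to 23% | 17 to 18% |
| 0.75 | iTAD overall score | −0.25 | 36% | 27 to 28% |

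The nominal rate is 5%, and almost all of these rejections lie in the 'worse baseline improves more' direction. At r = 0.85 and n = 24 the slope has that sign in 89% of null trials. Entering the psychological scale as three subscales (six predictors) gives 21% at r = 0.85.

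**If the retest correlation is lower.** The ICCs are reliability figures. The correlation over 5 to 8 weeks may be lower, but the article gives no value, so these are assumptions: at n = 24, r = 0.7 gives about 43%, r = 0.6 about 55% and r = 0.5 about 67%.

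**With both arms.** Under the same null, a group by baseline interaction (24 against 12) has mean slope 0.00 and p < 0.05 in about 5% of trials at r = 0.5, 0.75 and 0.85. With 19 against 10 it is also about 5%. Its precision is limited. At r = 0.85, in SD units, the standard error is roughly √[(1 − 0.85²)(1/23 + 1/11)] = √(0.2775 × 0.1344) = 0.19, so the 95% interval is about ±0.4.

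**The case against.** **It is exploratory.** Table 1 says so, section 2.13 speaks only of observing whether change is predicted, and section 3.2 concedes that secondary outcomes cannot support conclusions. This stands and limits the weight of the point. It does not remove it, because the label does not alter what the coefficient estimates.

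**The measure is not named.** Direct coupling needs baseline and change on the same measure, and the article does not say which is used. This stands as a condition. The same measure is the natural reading.

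**The planned model is already baseline-adjusted.** This stands. With baseline included, regressing change or the follow-up score gives identical coefficients for training time, sleep and psychological status. Only the baseline coefficient is in question.

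Three stronger readings are tempting, and the article does not support them.

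- *That the regression will show the artefact.* At the stated reliabilities, 64 to 86% of null trials with 24 completers give no significant baseline coefficient.
- *That the result would set eligibility for the full trial.* No section says so, and section 2.2 has no acuity criterion. This is inference.
- *That error in a self-reported log weakens the training-time estimate.* Section 2.12 does say that "training log data will be used to predict change in tactile acuity", but section 2.9 adds: "In the intervention group this will be cross-referenced to the iTAD software usage data for verification". The log is checked against recorded use, and nothing in the article shows the size of any remaining error.

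**Conclusion.** The concern holds for the baseline coefficient only. As written, the iTAD-arm regression is biased towards 'worse baseline improves more', and one arm cannot separate that bias from true effect modification. With no training effect and 24 participants, a nominal 5% test rejects in about 14 to 23% of trials at the reliabilities given for the two primary acuity measures, and in 36% at that for the iTAD score.

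These rates assume the same measure at both times, equal variances, the stated ICCs as retest correlations, and other predictors unrelated to acuity. Dropout lowers the rates, and a weaker retest correlation raises them. The group by time ANOVA of the primary outcome is not affected.

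**What to change.** In sections 2.12 and 2.13, assess baseline acuity as an effect modifier in all randomised participants. Regress the follow-up score on baseline, group and group × baseline, using the same named acuity measure throughout, and report the interaction with its confidence interval as exploratory. Using change as the outcome would give the same interaction coefficient.

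Keep baseline acuity in the iTAD-arm model as an adjustment when training time, sleep and psychological status are examined, and state that its coefficient will not be read as predicting response.

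This changes wording only, since both arms already have the measurements. The cost is precision: with 12 controls the interaction interval will be wide (about ±0.4 in SD units at r = 0.85), and a null result will not rule out a real dependence on baseline.

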### Experimental group

2.7

Participants allocated to the experimental group will undergo four weeks of in-home tactile acuity training with the iTAD in addition to their usual physiotherapy care. The iTAD consists of a wearable neoprene collar, containing 12 hemispherical nodes, each enclosing a vibrotactile stimulator (see Fig. 2; a full description has been published previously [17]. The nodes contact the back of the neck and are wirelessly connected to tablet computer with a custom-written software application. The application triggers vibrotactile stimulations, records the user responses, provides feedback and calculates accuracy scores. Training consists of two types of (serious) games: The *localisation game*, where users indicate the location of a single vibration by selecting the corresponding location on the tablet; and the *orientation game*, where users indicate the direction of a second vibration, relative to a first, by selecting the corresponding arrow. The explanation given to participants relating to how iTAD may improve symptoms is standardised (See Appendix 1).

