### Primary outcome measures

2.10

Tactile acuity measures will be assessed prior to the intervention (baseline), and at mid-treatment, 5-week follow-up (i.e., within 1-week of treatment completion and 5-weeks after commencement), and 2-month follow-up (i.e., 2-months after commencement) (See Table 1). Data relating to feasibility will be collected throughout the study.

**Table 1 tbl1:** Outcomes measures.

	Domain	Measures	Timepoints
Primary outcomes	Tactile acuity	Two-point discrimination Locognosia	1,2,3,4
			1,2,3,4
	Feasibility	Recruitment rates, adherence (training duration), dropouts Bang's Blinding Index Perceived treatment credibility (Credibility Scale)	Throughout
			4
			*1
Secondary outcomes	Pain Intensity	Pain intensity: 0–10 NRS current, average & worst pain in the past week	1,2,3,4
	Pain spread	Self-indicted on body chart	1,2,3,4
	Tactile acuity	iTAD overall score	1,2,3,4
Exploratory outcomes	Perceived change	Global Perceived Effect (GPE)	2,3,4
	Disability	Neck Disability Index	1,2,3,4
	Tactile acuity	iTAD sub-scores	1,2,3,4
Exploratory predictors	Training hours	Training log	4
	Sleep	Insomnia Severity Index	3
	Psychological	Depression Anxiety & Stress Scale	1
	Baseline measures	Tactile acuity	1

*Time points: 1 = baseline, *1 = three days into the intervention, 2 = mid-treatment, 3 = 5-week outcome assessment (within 1-week of intervention completion), 4 = 2-month outcome assessment.

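### Section 2.13 enters baseline sleep as a predictor, but Table 1 schedules the Insomnia Severity Index only at the 5-week, post-treatment assessment

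*Protocol article*

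**What the plan says.** Section 2.13 (Data analysis) describes a multiple linear regression in the iTAD group. The outcome is change in tactile acuity. The predictors are time spent training, baseline tactile acuity, "baseline sleep (Insomnia Severity Index") and psychological status.

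Table 1 (in section 2.10) gives the schedule. Under exploratory predictors, the sleep row reads "Sleep Insomnia Severity Index 3", and the key reads "3 = 5-week outcome assessment (within 1-week of intervention completion"). The row directly below reads "Psychological Depression Anxiety & Stress Scale 1", where 1 is baseline.

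Section 2.12 (Exploratory outcomes and predictor variables) gives the reason for including sleep: "Since the training effect may be affected by factors such as sleep". It sets no separate time for the questionnaire. It says that the listed variables "will be used to predict change in tactile acuity (for assessment timepoints see Table 1").

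Section 2.7 fixes the length of treatment: participants in the experimental arm "will undergo four weeks of in-home tactile acuity training with the iTAD".

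**The concern.** The analysis text needs a sleep score taken before training, and the schedule provides one only after training has ended. These are two incompatible times for one variable, not a detail left to a fuller document.

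The order of measurement decides what the regression coefficient means. A score taken before training can be read as a candidate predictor of response. A score taken after training may have been changed by the training itself, or by a change in pain over the same weeks. An association with change in acuity could then run in either direction. Section 2.12 says the exploratory outcomes are there mainly to inform a future trial, so a mislabelled predictor could be carried into that trial's design.

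The loss would also be permanent. A baseline questionnaire that was not given cannot be collected later, and no imputation model can supply a variable observed in nobody.

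**Working it through.** No arithmetic applies: no stated power, sample size or significance level depends on this variable. The check compares what section 2.13 requires of each named predictor with what Table 1 schedules.

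| Predictor in section 2.13 | Timing implied by section 2.13 | Time point in Table 1 | Match |
|---|---|---|---|
| Time spent training | Accumulates over treatment | 4 (2-month) | Yes; it can be totalled only after training |
| Baseline tactile acuity | Baseline | 1 | Yes |
| Sleep (Insomnia Severity Index) | Baseline | 3 (5-week) | **No** |
| Psychological status (Depression Anxiety & Stress Scale) | Baseline or unstated, depending on how far the word baseline carries | 1 | Yes |

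1. **Is time point 3 after treatment?** Yes. Training lasts four weeks (section 2.7). Section 2.10 places this visit 5 weeks after commencement, within a week of treatment completion.

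2. **Does any other text schedule a baseline score?** No. Section 2.12 defers to Table 1, and the number of baseline Insomnia Severity Index assessments in Table 1 is 0. Section 2.12 calls the instrument a scale rather than an index; I take it to be the same questionnaire.

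3. **Could the table have been damaged when the text was extracted?** This is unlikely. The four exploratory-predictor rows are intact, with time points 4, 3, 1 and 1 in order, and the key is legible.

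4. **How many participants are affected if Table 1 is followed?** All of them: the target is 24 + 12 = 36 (section 2.5), of whom the 24 in the iTAD arm are those the regression uses.

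5. **Would sleep be measured at the same visit as the outcome?** This depends on a choice that section 2.13 does not state. Acuity is measured at time points 1 to 4, and the visit that defines change is not named. If change runs from baseline to week 5, sleep and the end-point of the change are recorded at the same visit. If it runs to 2 months, sleep comes before the final acuity measurement. In both cases the sleep score is post-treatment.

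6. **What else uses the score?** Nothing that bears on the main conclusions. The ANOVA in section 2.13, the calculation in section 2.5 and the eight feasibility cut-offs in section 2.10 do not involve it.

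**The case against.** The best defence is that this is a one-digit slip in a condensed table and that the questionnaire will in fact be given at baseline. The article cannot exclude that. A reader might infer from Table 1 that the baseline data will certainly be missing, but the article does not support so strong a reading. It shows two statements in conflict, and the loss follows only if the time point 3 entry is what staff follow.

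The slip could also be in section 2.13. Section 2.12 attaches the word baseline to tactile acuity but not to the insomnia questionnaire, and its rationale could cover sleep around the training period. Time point 3 might then be intended. Even so, the score would not be baseline sleep, and section 2.13 would need correcting.

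Two other inferences go too far. One is that sleep is necessarily measured alongside the outcome, which holds only if change is taken to week 5. The other is that sleep is the only predictor recorded after treatment: training hours are listed at time point 4, so two of the four are. Training hours are legitimately post-baseline and are not labelled otherwise, so they do not excuse the sleep row.

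Finally, the regression is exploratory and confined to one arm. That limits the importance of the point but does not remove the contradiction.

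**Conclusion.** The point holds as an internal inconsistency between the schedule and the analysis text. Section 2.13 specifies a baseline variable that Table 1 does not schedule at baseline, and section 2.12 makes Table 1 the reference for timing.

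If Table 1 is followed, the stated regression cannot be run as described. One of its four named predictors would be replaced by a post-treatment score that may reflect the effects of training or of pain change. It could not be read as baseline sleep predicting response. If the questionnaire is in fact given at baseline, the harm shrinks to an error in a published table.

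The effect stays within one exploratory regression with a target of 24 participants. The correction is still worth making, because it costs little and a missed baseline measurement cannot be recovered.

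**What to change.** Reconcile Table 1 with section 2.13.

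- **Preferred:** list the Insomnia Severity Index at time point 1 in Table 1 and use that score in the regression. This is the only option that keeps the analysis as stated, and it agrees with the rows for psychological status and baseline acuity. Keep time point 3 as well only if change in sleep is of interest.
- **If only time point 3 is collected:** delete the word baseline before sleep in section 2.13, and report the score as a post-treatment correlate of change in acuity rather than a predictor of response.

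In either case, use one name for the instrument in sections 2.12 and 2.13 and in Table 1.

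The cost of the first option is a table correction and one questionnaire moved to a visit that already takes place. It adds a questionnaire only if time point 3 is kept too. The second option costs a change of wording and gives up the baseline question. The first has to be in place before participants pass their baseline visit; for those who already have, only the second remains.
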